## Background

Differentiation between Parkinson’s Disease (PD) and the various forms of atypical parkinsonism (AP) can be difficult, especially early in the disease course. This is due to overlap in clinical symptoms, certainly when the clinical picture has not yet developed fully. Forms of AP such as multiple system atrophy (MSA), progressive supranuclear palsy (PSP) or corticobasal syndrome (CBS) follow a more malignant disease course than PD and, unlike PD, generally do not respond well to dopaminergic therapy.

While difficult, a correct diagnosis is important for adequate disease management and patient counseling, as well as for research purposes. If, in the future, any disease-modifying therapy becomes available, then reliable diagnostic tools will be essential to distinguish PD from AP at the earliest possible stage.

Because there is not yet a reliable objective test for PD and AP, expert opinion remains the gold standard for the clinical diagnosis. In the hands of a movement disorders specialist, the diagnostic accuracy is higher (90%) compared to judgment by a general neurologist (76%) [1, 2]. Although the clinical diagnosis after several years of follow-up correlates highly with the neuropathological diagnosis upon post-mortem examination, the diagnostic accuracy of the initial diagnosis varies greatly, and can be as low as 30% [1, 3–5]. When a clinician has little doubt about the diagnosis, ancillary investigations have hardly any diagnostic value. But when the clinical picture is puzzling, which is often the case early in the disease course, reliable biomarkers are needed for accurate and early differentiation between PD and AP.

Brain MRI is nowadays part of the diagnostic workup of patients with suspected parkinsonism, mainly to exclude secondary causes of parkinsonism (e.g. tumor, hydrocephalus, multiple sclerosis, vascular parkinsonism). Conventional MRI can demonstrate abnormalities characteristic for various AP syndromes, such as putaminal or olivopontocerebellar atrophy in MSA, midbrain atrophy in PSP and asymmetric regional cortical atrophy in CBS.

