### Ancillary investigations

#### MRI

All patients will have a brain MRI at first presentation performed on 3 Tesla MRI scanner (Siemens Magnetom Trio, Erlangen, Germany) by a standardized scanning protocol. Conventional MRI sequences will include 3D T1 MPrage, T2 turbo-spin echo, T2 fluid attenuated inversed recovery (FLAIR), and proton density sequences. Advanced MRI sequences will include diffusion weighted imaging (DWI) and diffusion tensor imaging (DTI), SWI and rs-fMRI. All MRI scans will be evaluated in a systematic fashion by two neuroradiologists blinded for clinical symptoms and outcome. The presence of the following abnormalities on conventional MRI sequences will be scored using a diagnostic workstation (Agfa-Impax version 6.5.3, Gevaert, Mortsel, Belgium): atrophy and T2 hypo-intensity of the putamen, putaminal rim sign, frontal lobe and parietal lobe atrophy, lateral, third and fourth ventricle dilatation, midbrain and pontine atrophy, hummingbird sign, atrophy of the cerebellum and cerebellar vermis, atrophy of the medulla oblongata, T2 hyper-intense signal changes of the middle cerebral peduncle and hot cross bun sign, dilated perivascular spaces, lacunar infarctions and white matter changes. Advanced imaging sequences will be analyzed by dedicated software packages, including ‘Functional MR Imaging of the Brain Software Library‘(FSL, University of Oxford, United Kingdom) and ‘Statistical Parametric Mapping’ (SPM, Trust Centre of Neuroimaging, London, United Kingdom).

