### Statistical analysis

For our first objective, the estimated initial diagnosis by the movement disorder specialist, neuroradiologist and neurochemist respectively will be compared to the reference diagnosis (after three years follow-up). Sensitivity, specificity and Kappa (k) are calculated. Next, the Net Reclassification Index (NRI) is calculated, which gives the proportion of participants correctly (re-)classified as having PD or AP. NRI values will be calculated for MRI and CSF *following* the classification by a movement disorder specialist [40].

For our second objective, descriptive data will be generated for all variables. Continuous variables will be presented as means ± standard deviations or medians. PD patients will be compared with AP patients using a Student’s t or Mann-Whitney U test, whichever appropriate.

Dichotomous variables will be compared using Chi-square test or Fisher exact test, whichever appropriate. A *p*-value of < 0.05 will be considered significant (two-sided).

For each diagnostic strategy (e.g. clinical evaluation, MRI and CSF respectively) blockwise logistic regression with stepwise forward model selection will be used to identify parameters with optimal diagnostic power. For each model ROC-curves and C-statistics are calculated.

Data management and analysis will be performed using IBM SPSS Statistics 22 (IBM Corp, Armonk, NY, USA).

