### Sample size calculation

This study is exploratory in nature. We estimate that a minimum of 30 AP and 30 PD patients will be needed to evaluate the diagnostic value of the three diagnostic strategies (clinical evaluation by a movement disorder specialist, MRI and CSF biomarkers). In our previous cohort study of patients with parkinsonism 60% of patients had a diagnosis of AP [34]. 30% of patients did not complete the follow-up period of 3 years, mainly because the participant had deceased or was too severely affected, the majority of which was diagnosed with AP (33 out of 46 drop-outs). Therefore, we estimate that approximately 100 participants will be needed to assess the diagnostic accuracy of the different diagnostic tests.

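### Forward logistic regression for the MRI signs has no finite estimate for any sign seen in some AP patients and in no PD patient, which is possible with about 30 PD patients

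*Protocol article*

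**What the plan says.** The Statistical analysis section of the protocol article says that, for each of the three strategies, "blockwise logistic regression with stepwise forward model selection will be used to identify parameters with optimal diagnostic power". ROC curves and C-statistics follow for each model. The software is fixed: "Data management and analysis will be performed using IBM SPSS Statistics 22". No penalised or exact variant is named, so the natural reading is ordinary maximum likelihood. The selection criterion (Wald, likelihood ratio or other) is not stated.

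The MRI section describes the conventional-MRI inputs as binary: "The presence of the following abnormalities on conventional MRI sequences will be scored". The list includes the putaminal rim, hummingbird and hot cross bun signs and putaminal, midbrain, pontine and cerebellar atrophy. It also includes ventricular dilatation, dilated perivascular spaces, lacunar infarctions and white matter changes. The Background says of some such findings that "Conventional MRI can demonstrate abnormalities characteristic for various AP syndromes", naming putaminal, olivopontocerebellar, midbrain and asymmetric cortical atrophy.

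The Sample size calculation states that "a minimum of 30 AP and 30 PD patients will be needed", to be reached from roughly 100 enrolled.

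**The concern.** A binary sign present in some AP patients and in no PD patient produces quasi-complete separation. The logistic likelihood keeps rising as the coefficient grows, so there is no maximum. Software stops at its iteration limit and prints a large coefficient with a huge standard error, and the Wald p-value goes towards 1.

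The models exist to find the variables that best separate PD from AP, which is the secondary objective, so the selected set is itself a result. A sign that is perfectly specific in the sample is the kind of variable the search is meant to find. Whether it survives would depend on the removal criterion rather than on the data. This is a different matter from over-optimism after stepwise selection: here the estimate itself is undefined.

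**Working it through.** **Step 1. Are about 30 PD patients to be expected?** Inputs from the Sample size calculation and Discussion: 100 enrolled, 60% AP, 30% lost, 33 of the 46 drop-outs AP (so 13 PD), previous cohort of 156. The 30 + 30 has no formula behind it, so the check is whether 100 enrolled delivers 30 PD patients.
- Uniform loss: 100 × 0.40 × 0.70 = 28.0.
- 60% AP at enrolment: 156 × 0.40 = 62.4 PD with 13 lost, so 40 × (1 − 13/62.4) = 31.7.
- 60% AP among completers: 110 × 0.40 = 44 PD, so 44/156 × 100 = 28.2.

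All three are within two patients of 30. Table 1's MRI exclusions could lower the number available to the MRI model.

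**Step 2. What happens with an empty PD cell?** Illustrative table: 6/30 AP carriers, 0/30 PD carriers.
- Newton-Raphson coefficient at 5, 10, 20 and 30 iterations: 6.4, 11.4, 21.4, 31.4. It rises by about one per step and does not converge.
- At 20 iterations the standard error is about 16,400, so z = 21.4/16,400 = 0.0013 and Wald p = 0.999.
- Score test: 60 × (6 × 30)² / (30 × 30 × 6 × 54) = 6.67, p = 0.010.
- Likelihood-ratio test: 8.99, p = 0.003.
- Fisher's exact test: 2 × C(30,6)/C(60,6) = 0.024.

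Three tests see the association; the Wald test alone does not. A sign with 4/30 AP carriers already has score p = 0.038, so it could enter at a 0.05 level (assumed; no entry level is stated for the selection).

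**Step 3. How likely is an empty PD cell for one sign?** P(no carriers in 30 PD) = specificity^30. The document gives no specificity, so the values are assumptions.

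| Specificity | P(0 of 30) |
|---|---|
| 90% | 4% |
| 95% | 21% |
| 97% | 40% |
| 99% | 74% |

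It passes one half only when specificity exceeds 0.5^(1/30) = 97.7%.

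**Step 4. How likely is it for at least one sign?** Take eight independent signs with AP frequencies f evenly spaced over a range, 30 patients per group, and count a sign with no PD carrier and at least four AP carriers:

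P = 1 − Π[1 − specificity^30 × P(Binomial(30, f) ≥ 4)].

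| Assumed AP frequency | 90% | 95% | 97% | 99% |
|---|---|---|---|---|
| 3–10% | 5% | 23% | 40% | 63% |
| 10–35% | 25% | 79% | 96% | >99% |

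(The last four columns are assumed specificities.) The number of signs, their frequencies and their independence are all assumptions.

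**Step 5. What does penalised likelihood give?** For a single binary predictor, Firth's method equals adding 0.5 to each cell. For 6/30 against 0/30 the odds ratio is 6.5 × 30.5 / (24.5 × 0.5) = 16.2, log odds ratio 2.78, and the fitted AP probability for carriers is 6.5/7 = 0.93 instead of tending to 1.

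**The case against.** The strongest reply is that the selection criterion, thresholds and a fallback for sparse cells normally sit in an analysis plan, which is not shown, and that nothing here excludes penalised fitting. That stands as far as the missing details go: their absence is no error. But the article does fix a method and a package, and that choice, read naturally, fits sparse binary inputs poorly.

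Second, the consequence is limited. The outputs named for these models are ROC curves and C-statistics, which remain computable under separation (0.60 for the single sign in Step 2: (6 × 30 + 0.5 × 24 × 30)/900). The plan also gives descriptive data and chi-square or Fisher tests for every dichotomous variable, so a reader who infers that the sign would vanish from the results goes too far. This largely stands. It is not a full safeguard: at 4/30 against 0/30 Fisher's test gives 2 × C(30,4)/C(60,4) = 0.11. And a C-statistic describes whichever set was selected; it does not show that the selection was sound.

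Third, a reader might infer that the signs were chosen because they mark AP and will therefore usually be absent in PD. The MRI section gives no reason for its list, and several entries need not be rare in PD. The Background adds that these abnormalities often occur late, while entry requires under three years' disease and excludes patients with probable MSA, PSP, CBS or VP, so AP carriers may be few as well. In the other direction, the neurologists who set the reference diagnosis see the conventional MRI, which could lower PD carriage of AP-type signs. Neither influence can be quantified from the document.

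**Conclusion.** The point holds in conditional form. If a sign has some AP carriers and no PD carrier, the prescribed regression has no finite estimate for it, and its selection turns on an unstated criterion. With about 30 PD patients this is a real possibility, but its probability is not known: Step 4 runs from 5% to over 99% across the assumptions shown, so calling separation near-certain is not supported. Treating rim, hummingbird and hot cross bun signs as AP-type is general knowledge; the Background does not name them.

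The reach is the variable-selection models under the secondary objective of a study that describes itself as exploratory. Sensitivity, specificity, kappa and NRI rest on the raters' diagnoses and are unaffected. Separation has not been shown for the clinical or CSF models, and most CSF variables are concentrations, so a demand for penalised fitting in every model would go beyond the evidence. The change is worth making because it is cheap and needs no new data.

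**What to change.** In the Statistical analysis section, state that the MRI model, and any other strategy model containing a binary predictor with an empty cell in the PD-by-AP table, is fitted by Firth penalised-likelihood logistic regression, with penalised likelihood-ratio tests and profile-likelihood intervals. State that Wald tests are not used for entry or removal. Showing each selected sign's PD and AP counts beside its estimate would help; the planned descriptive tables already supply them.

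Cost: a few sentences and a routine outside stock SPSS 22, such as R or an SPSS extension. Odds ratios are slightly shrunk, and predicted probabilities are pulled slightly towards 0.5.

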### Sample size calculation

This study is exploratory in nature. We estimate that a minimum of 30 AP and 30 PD patients will be needed to evaluate the diagnostic value of the three diagnostic strategies (clinical evaluation by a movement disorder specialist, MRI and CSF biomarkers). In our previous cohort study of patients with parkinsonism 60% of patients had a diagnosis of AP [34]. 30% of patients did not complete the follow-up period of 3 years, mainly because the participant had deceased or was too severely affected, the majority of which was diagnosed with AP (33 out of 46 drop-outs). Therefore, we estimate that approximately 100 participants will be needed to assess the diagnostic accuracy of the different diagnostic tests.

### Loss to follow-up

In case patients opt to withdraw from the study or are no longer able to participate, the investigator will try to obtain a final interview and neurological examination if possible. When loss to follow-up is greater than 20%, analysis will be done to check for associated biased effects.

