### Assessment of diagnoses

Before inclusion, the referring neurologist will be asked to establish the probable diagnosis based on routine clinical examination. Specifically, a level of diagnostic (un) certainty will be indicated on a scale of 0–100. After inclusion, a movement disorder expert will also be asked for the diagnosis and level of certainty based on the clinical evaluation; a neuroradiologist makes the diagnosis based on imaging findings and a neurochemist based on CSF analysis.

The final clinical diagnosis will be established after three years of follow-up in consensus by two independent neurologists specialized in movement disorders, and this will serve as the “silver standard” reference diagnosis. This reference diagnosis will be based on the clinical data at baseline, the disease course after 3 years follow-up and with adherence to the following international clinical criteria: Movement Disorder Society clinical diagnostic criteria for PD [35], Gilman criteria for MSA [36], the movement disorder society criteria for PSP [37]**,** Armstrong criteria for CBS [38] and Zijlmans criteria for vascular parkinsonism [39]**.** These neurologists will be blinded for the results of the ancillary investigations, except for the conventional MRI because this is part of routine procedures in clinical practice. See Fig. 1 for a flowchart of the study design.

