## Discussion

A major unmet need in the diagnostic workup of parkinsonian disorders is a diagnostic tool to differentiate the various forms of parkinsonism when the clinically based uncertainty is high. This study is especially designed to provide directions for the neurologist in daily practice when the clinical picture of parkinsonism is puzzling.

Recently, we completed a similar prospective study of 156 consecutive patients with parkinsonism, but with an initially uncertain diagnosis [34]. All patients underwent extensive clinical testing and the following ancillary investigations: routine brain MRI; 123I-iodobenzamide single photon-emission computed tomography (IBZM-SPECT); CSF analysis; and anal sphincter electromyography (EMG).

We have shown that clinical tests such as tandem gait analysis and the axial UPDRS sub-score had a high predictive value to discriminate between PD and AP [34]. NFL and tau in CSF differentiated MSA from PD and tau and p-tau protein were elevated in CBS. Nonetheless, none of the ancillary investigations, (routine brain MRI, IBZM-SPECT, CSF analysis and anal sphincter EMG) was superior to the clinical judgment in differentiating parkinsonian syndromes [34].

However, diagnostic uncertainty in this previous cohort study was defined as being present when the neurologist who referred the patient was uncertain about the diagnosis (even when the patient fulfilled the probable criteria for one of the parkinsonian syndromes). Furthermore, patients from all disease stages were included. Therefore, the proportion of patients in an early disease stage and with an actual uncertain diagnosis was relatively small.

For that reason, the a priori chance that ancillary investigations would be of additional value was limited. Moreover, no advanced MRI techniques were used. Thus, we designed this present study to assess the diagnostic value of ancillary investigations in a population of patients with parkinsonism and an unclear clinical picture at the beginning of their disease course. We included the judgment of a movement disorder expert in the baseline examinations to compare its added diagnostic value to the various ancillary investigations. As ancillary tests, we chose brain MRI (both conventional and advanced MRI techniques) and CSF collection because of their potential to reveal new biomarkers for differentiating PD from AP based on developments over the past decade.

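### About 30% loss, concentrated in AP, is expected, but the plan does not say whether non-completers get a reference diagnosis, and its only analytic response is a check above 20%

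*Protocol article*

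**What the plan says.** All references are to the protocol article.

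- **Reference diagnosis.** Under Assessment of diagnoses: "The final clinical diagnosis will be established after three years of follow-up in consensus by two independent neurologists specialized in movement disorders". Outcome measures makes the PD or AP diagnosis at that time the primary outcome, and Statistical analysis compares every test with it. The Discussion defends this choice by the agreement between the three-year clinical diagnosis and neuropathology.
- **Expected loss.** Sample size calculation says of the previous cohort: "30% of patients did not complete the follow-up period of 3 years, mainly because the participant had deceased or was too severely affected". It adds that 33 of the 46 drop-outs had AP.
- **Sample size.** The requirement is that "a minimum of 30 AP and 30 PD patients will be needed to evaluate the diagnostic value of the three diagnostic strategies". After citing the AP share and the loss in the previous cohort, the section concludes: "we estimate that approximately 100 participants will be needed to assess the diagnostic accuracy of the different diagnostic tests".
- **Handling of loss.** Loss to follow-up has two sentences. The first says that, for patients who withdraw or cannot continue, the investigator will attempt a last interview and examination where this can be done. The second is: "When loss to follow-up is greater than 20%, analysis will be done to check for associated biased effects".

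**The concern.** By the plan's own account, loss depends on the target condition (AP more than PD) and on its severity (death, or being too ill). Patients lost for these reasons may also differ in how readily the baseline tests identify them. Accuracy measured only in those who reach three years would then describe a set that under-represents severe, fast-progressing AP. Sensitivity, specificity, kappa and the Net Reclassification Index are all exposed.

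The 20% trigger does not address this. It lies below the plan's own expected loss, so the check is the expected case, yet no action follows from a positive result. Below 20%, differential loss need not be examined at all. The last examination helps only some patients: it cannot be done after death and is often impractical in the very ill, and these are the two main causes of loss that the plan names.

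**Working it through.** **Inputs.** Previous cohort of 156 (Discussion). From Sample size calculation: 46 drop-outs, 33 of them AP; 60% AP; minimum 30 AP and 30 PD; planned N about 100. Assumption: the other 46 − 33 = 13 drop-outs had PD.

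**1. Reproduce the stated loss.** 46/156 = 29.5%, which matches the stated 30%. AP share of the drop-outs: 33/46 = 71.7%.

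**2. Loss by diagnosis.** The text does not say whether 60% AP refers to everyone enrolled or to completers, so both are shown.

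- *A, all enrolled:* AP 0.6 × 156 = 93.6 and PD 62.4. Loss is 33/93.6 = 35.3% of AP and 13/62.4 = 20.8% of PD.
- *B, completers:* 156 − 46 = 110 completers, so 66 AP and 44 PD. Adding drop-outs gives 99 AP and 57 PD. Loss is 33/99 = 33.3% of AP and 13/57 = 22.8% of PD.

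**3. What the sample size implies.** With no loss, 30 PD at a 40% share needs 30/0.4 = 75 patients. With loss, A gives 30/(0.4 × 0.792) = 94.7, so 95; B gives 30/(44/156) = 106.4, so 107. The plan shows no formula, but about 100 lies between these. Going from 75 to about 100 makes sense only if drop-outs are not counted on as evaluable.

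**4. Composition per 100 enrolled (A).** AP: 60 × (1 − 0.353) = 38.8. PD: 40 × (1 − 0.208) = 31.7. The AP share falls from 60% to 38.8/70.5 = 55%.

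**5. Loss at the trigger.** With 20 of 100 lost in the same mix, 20 × 33/46 = 14.3 are AP, or 14.3/60 = 24% of AP. The other 5.7 are PD, or 5.7/40 = 14% of PD. This loss would not set off the check.

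**6. Effect on sensitivity for AP.** Let d be the fraction of AP lost, Se_c the sensitivity in completers and Se_l the sensitivity in those lost.

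Se_all = (1 − d) × Se_c + d × Se_l, so Se_all − Se_c = d × (Se_l − Se_c).

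With d = 0.353 this is 3.5 points per 10-point difference (3.3 under B). The document gives no sensitivities, so the values below are assumed, with Se_c = 0.70:

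| Se_l (assumed) | Se_all (A) | Shift |
|---|---|---|
| 0.50 | 0.629 | −7.1 points |
| 0.70 | 0.700 | 0 |
| 0.90 | 0.771 | +7.1 points |
| 1.00 | 0.806 | +10.6 points |

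This assumes that no lost AP patient is recovered. If half are recovered at random in the 0.90 row, 38.8 retained and 10.6 recovered patients give (38.8 × 0.70 + 10.6 × 0.90)/49.4 = 0.743. The gap to 0.771 is then 2.8 points.

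**The case against.** A reader might infer that the plan analyses only three-year completers, discards the MRI and CSF data of everyone else, and so measures accuracy in slow progressors alone. The document does not say this. It nowhere excludes non-completers, and it plans a last examination for those who stop. Under Follow-up, patients stay with their own neurologist and receive yearly questionnaires. The same team could evidently classify drop-outs before, since it reports how many had AP. Even on the figures above, about 65% of AP patients are retained. Completers as the analysis set is an inference from the sample size and the three-year reference.

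It is also tempting to call crossing the trigger near certain. The binomial chance of more than 20 losses in 100 is 98% at 29.5%, but the Discussion says the earlier cohort covered all disease stages. At assumed rates of 25%, 20% and 15%, the chance is 85%, 44% and 7%. The sensitivity contrasts are likewise hypothetical.

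Two further objections carry weight. An article may leave analysis sets and imputation to a full protocol or SAP, and this study calls itself exploratory. And a last-available diagnosis is less mature: the Background notes that initial diagnoses can be as little as 30% accurate, so including them trades selection for misclassification.

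These points limit the claim but do not remove it. The text does state a response to loss, and that response is inadequate for the loss it expects: a check removes no bias, and no examination is possible after death. If early diagnoses do count, references of different maturity are mixed without a rule; if they do not, the analysis set is selected. The trade-off is a reason to grade certainty and report both analyses.

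**Conclusion.** The concern holds as a well-founded risk, not as something the document fixes. The plan expects about 30% loss driven by death and severity, ties the reference to three years, does not say whether an earlier diagnosis serves, and answers with an unspecified check above a threshold lower than its own expected loss. Followed as written, it would probably estimate accuracy in a set that under-represents severe AP.

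The implied size is a loss of 33-35% of AP and 21-23% of PD, and a shift in AP sensitivity of about 3.5 points per 10-point difference between lost and retained AP patients. This rests on the earlier cohort's rates carrying over, on the 13 remaining drop-outs being PD, and, for the shift, on no lost patient being recovered. The direction cannot be determined from the document.

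**What to change.** Replace the 20% trigger with a rule that applies at any loss rate:

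1. The two-neurologist panel, under the same blinding, assigns a last-available reference diagnosis with a certainty grade to every enrolled patient who dies or drops out. Sources are the final visit where there was one, the yearly questionnaires and the treating neurologist's records, with any test results to which the panel is blinded removed.
2. These patients enter the main accuracy and Net Reclassification Index analyses. Three-year completers are reported as a sensitivity analysis.
3. Patients who cannot be classified are handled by weighting or multiple imputation on baseline variables, such as the expert's diagnosis, its certainty and disease severity.
4. Loss is reported by diagnosis.

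The cost is a records request to treating neurologists, one paragraph in the protocol and modest analysis work. The records should be requested early, because those of deceased patients become harder to obtain. The downside is that last-available diagnoses are less certain than three-year ones. The certainty grade and the completer analysis make that visible.
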